#### 2.6.1. Criteria for the ESD operators

All endoscopists performing ESD must be a principal investigator or sub-investigator; must have performed at least 5 colorectal ESD procedures; and must have performed at least 1 colorectal ESD procedure using the S-O clip.

#### 2.6.2. ESD procedure using the S-O clip

A procedural endoscope will be inserted into the colon. After local injection around the lesion, a mucosal incision will be made and submucosal dissection will be performed. If necessary, an additional local injection into the submucosal layer will be performed with the needle or high-frequency knife. After a circumferential incision, the S-O clip will be placed on the lesion. The ZEOCLIP will be used to pull the spring portion of the S-O clip and secure it to the contralateral wall. The number of clips used for traction is indeterminate. If the first S-O clip does not fit properly or detaches during the procedure, it may be reattached as appropriate. After applying traction, the lesion will be dissected and excised while visualizing the submucosal layer. Traction of the lesion is expected to facilitate visualization of the submucosal layer and allow complete resection.

#### 2.6.3. Conventional ESD procedure

A procedural endoscope will be inserted into the colon. After local injection around the lesion with a needle, mucosal incision and submucosal dissection will be repeated, with gravitational traction provided by a tip hood attached to the endoscope. Local injection into the submucosal layer with a needle or high-frequency knife will be performed when necessary. Submucosal dissection should excise the lesion without other traction devices.

### 2.7. Primary endpoint:

The primary endpoint of this study will be procedure time, defined as the interval from the start of local injection into the submucosal layer until the completion of dissection.

### 2.8. Secondary endpoints:

Several secondary endpoints will be evaluated. The first is the incidence of procedural complications (i.e., intraoperative perforation, delayed perforation, post-bleeding, PECS), defined as the ratio of the number of procedure-related complications to the total number of patients in the efficacy analysis population. PECS in the absence of obvious perforation will be defined as localized tenderness plus fever > 37.6°C, white blood cell count > 10.000/mm^3^, or C-reactive protein concentration ≥ 0.5 mg/dL within 6 hours after ESD. Posterior hemorrhage will be defined as a ≥ 2 g/dL decrease in Hb concentration or overt bleeding requiring endoscopic hemostasis, but not as a small amount of blood in the stool. Perforation will be defined as a total tissue defect that allows free passage to the body cavity, regardless of the presence of free air on radiographic examination.

Other secondary endpoints will include the *en bloc* resection rate, defined as the percentage of lesions resected en bloc without segmental resection; and the cure resection rate, defined as the percentage of resected specimens that meet all the following criteria on pathological evaluation: negative horizontal and vertical margins (complete resection); histological type such as papillary adenocarcinoma, ductal adenocarcinoma, or adenoma; evaluation of intramucosal carcinoma or submucosal invasion showing that the distance of submucosal invasion is < 1000 μm; and negative for lymphovascular and vascular invasion. Another secondary endpoint in patients who undergo ESD with the S-O clip will be the time from the start of traction with the S-O clip to the completion of detachment. An additional secondary endpoint will be the conversion rate, defined as the percentage of patients undergoing conventional ESD who required S-O clip placement during the procedure and the percentage of patients undergoing ESD with the S-O clip who required S-O clip removal. Finally, the incidence of adverse events will be evaluated.

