## 2. Methods/design

### 2.1. Study aims and design

This prospective randomized clinical trial involving 4 medical institutions in Japan was designed to compare the efficacy and safety of the ESD procedure using the S-O clip with conventional ESD in patients with colorectal epithelial neoplasia.

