### 3.2. Statistical analysis

#### 3.2.1. Evaluation of the primary endpoint.

Multiple regression analysis will be performed using procedure time (i.e., from the start of localization to the completion of detachment) as response and allocation group and allocation factor as covariates. Point estimates, 95% confidence intervals, and *P* values for between-group differences will be calculated. In addition, summary statistics (mean, standard deviation, minimum, median, maximum) of treatment duration will be calculated for each group or ESD surgeon (trainee/expert).

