#### 3.2.2. Evaluating secondary endpoints.

The complication rate will be defined as the rate of complications associated with the procedure. The frequencies and percentages of complications associated with the procedure, as well as the batch resection, cure, conversion, and adverse event rates will be tabulated for each group. Summary statistics (mean, standard deviation, minimum, median, maximum) from the time of S-O clip traction to the completion of dissection will be calculated for the S-O clip group.

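### The complication rate divides a count of complications by a count of patients in an undefined efficacy set, and the planned by-group tables give no effect estimate for the promised safety comparison

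*Protocol article*

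**What the plan says.** Section 2.8 of the protocol article lists the incidence of procedural complications as the first secondary endpoint. Its components are "intraoperative perforation, delayed perforation, post-bleeding, PECS", and the rate is "defined as the ratio of the number of procedure-related complications to the total number of patients in the efficacy analysis population". The article does not define that population. PECS and perforation are kept apart by definition: "PECS in the absence of obvious perforation will be defined as localized tenderness plus fever" and further criteria.

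Section 3.2.2 returns to the endpoint: "The complication rate will be defined as the rate of complications associated with the procedure". It then plans frequencies and percentages of complications, "as well as the batch resection, cure, conversion, and adverse event rates will be tabulated for each group". It names no between-arm difference, interval or test. For procedure time, section 3.2.1 does: "Point estimates, 95% confidence intervals, and *P* values for between-group differences will be calculated".

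On purpose, section 2.1 says the trial "was designed to compare the efficacy and safety of the ESD procedure" with the clip against conventional ESD. The Discussion (section 4) says complication frequency will be compared between the techniques. The Conclusion (section 5) expects the trial to settle whether the clip is safer as well as more effective.

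**The concern.** Three things do not fit together.

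- **Units.** The numerator counts complications and the denominator counts patients. A percentage built this way reads as the share of patients harmed, but it is that only when nobody has two complications. Elsewhere in section 2.8 the conversion rate is worded per patient, so the article does use patient-level wording for another rate.
- **Population.** A complication rate is a safety outcome, yet its denominator is an efficacy set. If that set leaves out procedures that were not completed, it could leave out patients whose procedure ended because of a complication.
- **Output.** The stated aim and conclusion concern a comparison of safety. The stated analysis is a table per arm, which shows two percentages but neither the size of their difference nor its uncertainty.

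At stake is the endpoint that most directly carries the safety claim. The trial is open-label, so how to count patients with several events should be settled before the data are seen.

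**Working it through.** The article gives no expected rate, target difference or sample size for complications. Its only sample-size figures, 192 and 324 in section 3.1, are for procedure time. They reproduce with a difference of 104.1 − 85.2 = 18.9 minutes and the clip arm's SD of 52.3: a two-sided t-based calculation gives 95.4 and 161.9 per arm, rounded up to 96 and 162. They have no bearing on this endpoint.

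**Step 1: can one patient contribute more than one complication?** From the definitions in section 2.8:

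- PECS with obvious perforation: excluded by definition.
- Bleeding with PECS: possible, counts 2.
- Bleeding with perforation: possible, counts 2.
- Intraoperative perforation, delayed perforation and bleeding: possible as worded, counts 3.

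So the overlap is limited but not ruled out, and the ratio is not bounded by 1.

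**Step 2: by how much can the ratio differ from the share of patients affected?** Let N be the denominator, A the patients with at least one complication and E the complications. Then

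E/N = (A/N) × (E/A).

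The reported figure is the share affected multiplied by the mean number of complications per affected patient. The documents give no bleeding or perforation rate from which to estimate E/A, so the inputs below are assumptions:

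- No patient has two events: E/A = 1 and the two figures are identical.
- A = 15, E = 20, N = 100: reported 20%, affected 15%.
- A = 25, five of them with two events, so E = 30, N = 100: reported 30%, affected 25%, a relative excess of 30/25 − 1 = 20%.

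**Step 3: the denominator.** If k affected patients were left out of both counts, the share of patients affected would become (A − k)/(N − k), which is below A/N whenever A < N. If they stayed in the numerator but left the denominator, it would become A/(N − k), which is above A/N. The wording restricts only the denominator explicitly, so even the direction of any distortion is open. Whether k is above zero cannot be read from the article.

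**Step 4: what precision would a between-arm estimate have?** Allocation is 1:1 with 200 patients, so about 100 per arm. Counting each patient once and assuming the same true rate p in both arms, the 95% half-width of the risk difference is 1.96 × √(2p(1 − p)/100):

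| p | Half-width |
|---|---|
| 12.1% | 1.96 × √(2 × 0.121 × 0.879/100) = 0.090 |
| 20% | 1.96 × √(2 × 0.20 × 0.80/100) = 0.111 |
| 40% | 1.96 × √(2 × 0.40 × 0.60/100) = 0.136 |

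The outer rates are the PECS range that section 1 cites for colorectal ESD; 20% is an assumed intermediate value. None is a rate for the four-part composite.

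If the clip halved the rate (an assumption), power at two-sided 0.05 would be 32% from 12.1%, 51% from 20%, 72% from 30% and 88% from 40%. The half-widths would be 7.9, 9.8, 11.4 and 12.4 points.

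**The case against.** The strongest reply is that this is loose wording in a condensed article. The terms incidence and percentages suggest that affected patients may be meant. The PECS definition removes one of the main overlaps, and with no overlap nothing changes numerically. Section 3.1 describes 192 as a number for exploration, below the 324 for validation, and a trial of 200 may reasonably treat secondary endpoints descriptively. Analysis sets and intervals for secondary endpoints are often left to the full protocol or analysis plan, which are not shown.

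Much of that stands, and it rules out several stronger readings that a reader might infer:

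- *That the plan contains no safety comparison between arms.* Tables of complications and adverse events by group are a descriptive comparison. What is missing is an effect estimate with an interval.
- *That the complication rate will be inflated.* It will be only if some patients have two or more events; the examples above are illustrations.
- *That the efficacy set drops the patients with complications.* The article states no such exclusion, and the set could equal all treated patients. Section 2.6 allows a change of operator or technique so that procedures can continue. Adverse events are a separate endpoint without this restriction, and section 3.4 records them from the start of treatment.
- *That the half-widths measure the defect.* They describe what 200 patients can show, and correcting the definition would not change that.

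What the reply does not remove is the stated rule. Section 2.8 sets out a numerator and a denominator in different units, section 3.2.2 restates the rate without correcting it, and an efficacy set is named for a safety outcome. Tabulation alone is also a thin basis for the expectation in section 5, even though the abstract's Discussion is more cautious and says only that the question may be resolved.

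**Conclusion.** The point holds as a defect in a stated definition and a mismatch between analysis and conclusion. Followed literally, section 2.8 yields complications per patient, which exceeds the proportion of patients affected whenever one patient has more than one event and equals it otherwise. The size of any excess cannot be estimated from the documents; the example of 20% against 15% rests on assumed overlap, and zero excess is possible. The efficacy denominator is a risk that depends on a definition the article does not give.

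The planned output supports a descriptive comparison. It does not by itself support a conclusion that the clip is safer. With 100 per arm, equal true rates and each patient counted once, a risk difference would carry a 95% half-width of about 9 points at 12.1% and about 14 points at 40%. These use PECS rates as stand-ins for an unstated composite rate. The primary endpoint is unaffected.

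**What to change.** - Define the complication rate as patients with at least one of the four listed complications divided by all randomised patients in whom ESD was started, by allocated arm. Show each of the four components separately. If the total number of complications is also wanted, report it as a count, not as a percentage of patients.
- In section 3.2.2, replace the circular definition with this one and add the between-arm risk difference with a 95% confidence interval for the composite and for each component.
- Word the safety statements in sections 4 and 5 to match that precision, so that an interval compatible with no difference or with harm is not read as evidence that the clip is safer.

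The cost is a change of endpoint and analysis wording and a little extra analysis. It needs no further patients, procedures or data items.

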### 2.4. Exclusion criteria

Patients will be excluded if pre-operative examinations show indications of deep submucosal invasion; if the lesion is preoperatively diagnosed as a neuroendocrine tumor; if the tumor cannot be visualized in its entirety even with inversion; if the tumor crosses the anal canal, terminal ileum, appendix, or diverticulum; or if patients are eligible for ESD of ≥ 2 with colorectal tumors. Patients will also be excluded if their platelet counts are < 50,000/μL; if they are taking 2 or more antiplatelet agents or an anticoagulant other than warfarin; or if they are taking warfarin with a PT-INR ≥ 2.6, or a PT-INR ≥ 3.0 following mitral valve replacement surgery.^[13,14]^ Patients will also be excluded if they have serious complications in other organs, defined as an American Society of Anesthesiologists physical status ≥ 4; are pregnant; or are deemed ineligible for any other reason by the principal investigator or sub-investigator.

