### 2.6. ESD procedures

The endoscope will be inserted into the colon; after identifying the lesion, its periphery will be marked when necessary. Solution will be injected into the submucosa and submucosal dissection will be continued until completion. There were no restrictions regarding endoscopes, needles, hemostats, and hoods, although only the Dual Knife (Olympus) was allowed for marginal incisions and submucosal dissection. Upper endoscopy was allowed, depending on the situation. EMR on other polyps was allowed before or after ESD on the same day. To ensure patient safety, for patients in whom it is impossible to complete the procedure, the trainee could be replaced by a specialist, thus allowing the procedure to continue. Trainees assigned to a procedure that has lasted more than 60 minutes but who are unable to continue the assigned procedure will be allowed to switch to the other procedure. Physicians having difficulty completing conventional ESD within 60 minutes will be allowed use of the S-O clip midway through the procedure. Conversely, physicians having difficulty completing ESD with the S-O clip within 60 minutes, due to interference by the S-O clip, will be allowed to remove the clip. Antithrombotic medications will be withdrawn or replaced according to gastrointestinal endoscopic practice guidelines.^[7,15]^

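### The cure rate is taken over resected specimens, so a patient whose lesion is not resected leaves the denominator instead of counting as not cured

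*Protocol article*

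**What the plan says.** Section 2.8 (Secondary endpoints) states three rates on three different units:

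- **Complications**: the number of procedure-related complications over "the total number of patients in the efficacy analysis population".
- **En bloc resection**: "defined as the percentage of lesions resected en bloc without segmental resection".
- **Cure resection**: "defined as the percentage of resected specimens that meet all the following criteria on pathological evaluation". The criteria are negative margins, eligible histology, limited submucosal invasion and no vessel invasion.

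Three other sections bear on the point. Section 2.4 excludes patients "if patients are eligible for ESD of ≥ 2 with colorectal tumors"; the wording is garbled, but it appears to leave one ESD lesion per patient. Section 2.6 provides for difficult procedures: "for patients in whom it is impossible to complete the procedure, the trainee could be replaced by a specialist", so that the procedure can go on. It also allows a change of technique when 60 minutes have not sufficed. Section 3.2.2 tabulates frequencies and percentages of the cure rate for each group and states no test or between-group estimate.

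**The concern.** A lesion that is not resected is a failure to cure, but it yields no specimen. Under the stated denominator that patient is removed from the rate rather than counted as a failure. Whether a lesion is resected is known only after randomization and may depend on the technique: the article itself expects the clip to make dissection easier and complications fewer, and section 4 notes that perforation can lead to emergency surgery. Operators are also unblinded (2.5), so whoever judges that a procedure cannot continue knows the allocation. Other things equal, the arm with more failed resections would show the more flattering cure rate.

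A second ambiguity lies in the unit. Section 2.8 foresees segmental resection but does not say whether a lesion removed in pieces is one specimen or several.

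The abstract names cure among the outcomes, and the conclusion says the trial should settle whether the clip method is more effective. Readers will therefore compare the two tabulated cure rates, with or without a test.

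**Working it through.** The article gives no cure rate and no rate of unresected or piecemeal lesions, so there is no plan figure to reproduce. All counts below are assumptions, chosen to show direction and scale.

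**Inputs.** 100 patients per arm (200 patients, 1:1; sections 3.1 and 2.2), one ESD lesion each (2.4, as read above), and 85 curative resections in the arm (assumed).

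**Step 1: unresected lesions.** With u lesions not resected, the rate per patient is 85/100 = 85.0% whatever u is. The rate over resected lesions is 85/(100 − u).

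| u | Calculation | Rate over resected lesions |
|---|---|---|
| 0 | 85/100 | 85.0% |
| 2 | 85/98 | 86.7% |
| 5 | 85/95 | 89.5% |
| 10 | 85/90 | 94.4% |

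The rate rises with the number of failures. The values 2 to 5 serve as the illustration; 10 shows only how the formula behaves.

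**Step 2: the unit for piecemeal lesions.** If a lesion in pieces is one specimen, the rate does not move. If every piece were a specimen, with p piecemeal lesions of k pieces each, none counted as cured and no unresected lesions, the rate would be 85/(100 + p(k − 1)):

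- p = 5, k = 2: 85/105 = 81.0%
- p = 5, k = 3: 85/110 = 77.3%

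This runs opposite to step 1, and the two can cancel: with 5 unresected lesions and 5 piecemeal lesions in 2 pieces, 85/(95 + 5) = 85.0%. Step 2 applies only under one of two possible readings, so it measures the ambiguity and is not an expected error.

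**Step 3: effect on the contrast between arms.** Suppose one arm has 5 unresected and 82 cured, the other 3 unresected and 83 cured.

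- Per patient: 82.0% − 83.0% = −1.0 point.
- Over resected lesions: 82/95 − 83/97 = 86.3% − 85.6% = +0.7 point.

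The sign changes, but the shift is only about 1.7 points. The standard error of a difference between two rates near 84% with 100 per arm is √(2 × 0.84 × 0.16/100) = 0.052, about 5 points. A shift of this size is well inside sampling error.

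**The case against.** The strongest case on the other side has five parts.

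1. *Section 2.6 is not evidence of abandoned procedures.* The sentence on procedures that cannot be completed goes on to say how they continue. This stands: the section describes rescue routes, and no section reports or predicts lesions left unresected. It does not make them impossible, since operator replacement is stated for trainees and a change of technique does not guarantee completion. It does suggest that they may be few.
2. *Counting piecemeal lesions several times is only one reading.* This stands. A specimen can equally be the one reconstructed specimen per lesion, and the pathology criteria fit that use. A reader might infer multiple counting, but the text does not establish it. What remains is that the unit should be stated.
3. *The arms are compared as randomized.* A reader might infer otherwise from the specimen denominator. The document does not support that: section 3.2.2 tabulates by group, and nothing regroups patients by treatment received. Only the denominator is selected after randomization.
4. *The en bloc rate is sound.* This stands. Its base is lesions, so on its natural reading unresected and piecemeal lesions remain in it as failures. Nor do margins that cannot be assessed need a new rule in the cure rate, since a specimen must meet every criterion, including negative margins.
5. *A condensed article leaves such rules to the full protocol.* This would answer a complaint about a missing rule, for example the undefined efficacy analysis population. It does not answer this point, because the article states a denominator, and the stated denominator is the problem.

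**Conclusion.** The point holds in a limited form. As written, the cure rate leaves out any patient whose lesion is not resected, and so conditions on a post-randomization result that the technique can influence. It also differs in unit from the two neighbouring rates, although a patient denominator already exists in the same section. Whether a piecemeal lesion counts once or more is unsettled.

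The size depends on counts that the article does not give. On the assumption of 85 cured among 100, 2 to 5 unresected lesions would lift one arm's rate by 1.7 to 4.5 points (86.7 − 85.0 and 89.5 − 85.0). The contrast between arms moves less when both arms have such cases, and hardly at all if they are rare.

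Severity is minor. Cure is a secondary endpoint that is tabulated without a stated test, and the primary endpoint, procedure time, and the sample size are unaffected.

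**What to change.** In section 2.8, and correspondingly in 3.2.2, define the cure resection rate per patient (one ESD lesion each) in the allocated arm, with the same patient denominator as the complication rate. State that:

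- a lesion that is not resected counts as not cured, and failure to resect is not a ground for leaving the denominator;
- a lesion removed in pieces is counted once;
- the rate among resected lesions is given as a supplementary figure.

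The en bloc definition needs no change. The cost is a sentence in each section and no new data. The one downside is that the headline cure rate may look slightly less favourable than a rate over resected specimens.
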